### Data Management and Statistical Methods

#### Data Management and Dropout From Study

In order to enter all variables defined in the study protocol, standardized electronic case report forms will be prepared and administered. All questionnaires will be set up electronically and administered on a laptop. Data entry will only allow values in a valid range. Prior to data analyses, data will be checked for plausibility.

In this trial two different kinds of dropout will be defined: a study dropout and therapy dropout. A study dropout is defined as a participant who misses at least one of the main assessments (baseline, 8- or 16-week follow-up, see Figure 1). A therapy dropout is defined as a participant

who stops therapy before the initial session and a minimum of two movement retraining sessions,who stops therapy after the minimum number of sessions but before the therapy goal has been reached (typical reasons: low therapy adherence, external factors such as moving away, etc.), orwho no longer meets eligibility criteria (e.g., due to change in regimen of psychopharmacotherapy).

The reason for dropout must be documented by the therapist. Even if participants drop out of the treatment or become non-eligible during the course of the therapy, they will be encouraged to complete further follow-up assessments.

#### Sample Size, Power Calculations, and Interim Analyses

The power analysis for our trial was run with G^*^Power 3.1.9.4. In a previous trial, a physiotherapy for functional motor symptoms reached a moderate effect (*f* = 0.33) at 6-month follow-up on the SF-36 Physical Functioning subscale, our primary outcome (23). For this trial we conservatively assume a small group^*^time interaction effect (*f* = 0.10) under consideration of our three measurements and a test-retest reliability of *r* = 0.5. A power analysis for a mixed-effect ANOVA with an alpha error probability of 0.05 and a power of 0.80 results in an optimal total sample size of 164. A dropout rate of 5% is estimated based on our clinical experience and a recently completed trial that evaluated physiotherapy for individuals with FNSD (23). Accordingly a sample size of 172 participants is planned to be recruited.

We will, however, allow eight interim analyses every 22nd patient, conducted by a person who is independent of the day-to-day activities of the trial. Using the Lan-DeMets alpha spending function (55) we have gained appropriate boundaries or *p*-values for each interim analysis that would indicate a necessary stop and would allow an early conclusion of the trial (see Table 3). We used R 4.0.2 (56) and the ldbounds package (57) to gain Lan-DeMets boundaries. This approach helps to control for alpha-error accumulation with repeated interim analyses.

**Table 3 T3:** *P*-values (based on Lan-DeMets alpha spending function) indicating a necessary stop of the trial and needed sample size at each interim analysis.

**Interim analysis**	**Sample size**	***P*-value**
1	22	0.00000003
2	44	0.00009
3	66	0.001
4	88	0.005
5	110	0.013
6	133	0.024
7	155	0.036
8	172	0.050

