#### Statistical Analysis

Analyses will be based on intention-to-treat principles and will be carried out at the end of the last follow-up assessment. We will apply a linear mixed-effect model with baseline adjustment with main effects (fixed effect) for time (level 1, contrasts to baseline at 8- and 16-week follow-up) and group (level 2), group-by-time cross-level interaction term (8- and 16-week follow-up), and a generalized covariance matrix to account for dependency among observations. In order to deal with missing values, maximum likelihood estimation will be applied. Patterns of missing values will be assumed to be random. The outcomes of interest will be the group-by-time interaction at week 8 (hypothesis 1 and 2), and at week 16 (hypothesis 3). Effect sizes (Cohen's d) with 95% CI of changes between baseline and 8- and 16-week follow-up, as well as of between-group differences at 8- and 16-week follow-up will be investigated. Further sensitivity analyses will be conducted depending on the dropout rates and pattern of dropout reasons. For this purpose the linear mixed-effect models described above will be rerun for defined subgroups of the total sample (e.g., for participants with complete datasets only). To test for moderation (exploratory research question) we will add the moderator variable to the linear mixed-effect model described above (level 1: time; level 2: group) and will analyze a 3-level interaction. A significance level of 5% will apply to all analyses. Statistical analyses will be conducted with SPSS.

A limitation of group analyses is that it provides no information about the relative proportions of participants who did or did not respond to a treatment, which is based on a set standard. In accordance with recommendations by the Initiative on Methods, Measurement, and Pain Assessment in Clinical Trials (58), we will compare the distribution of participants with an improvement of at least 30 or 50%, no change, or deterioration on the primary outcome between the study groups with χ^2^-tests. Groups will be compared regarding adverse therapy effects, measured with the Inventory for the Assessment of Negative Effects of Psychotherapy, with independent sample *t*-tests and χ^2^-tests. To assess interrater reliability of the treatment fidelity ratings, intraclass coefficients (two-way random model with measure of agreement) for each item will be computed.

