Besides the strengths, we anticipate several limitations. We have already discussed risks of bias and have implemented tools to reduce these risks. There are additional challenges that we anticipate with implementing the study procedure. First, recruiting from one hospital can limit the representativeness of our sample and can hamper the potential to gain the optimal sample size. The institution where we will conduct our trial covers the neurological rehabilitation of a substantial part of the NZ population, which will ensure our sample is largely representative for the region. We first want to ensure the feasibility of our trial at this site before considering the potential to extend the trial to at least one other site. With a priori planned interim analyses, we will regularly check if the conservative estimation of our optimal sample size will need correction. Second, the design of our active control intervention has several advantages mentioned above. Nonetheless, we have to expect indirect therapeutic effects of our active control treatment (e.g., incidental change in beliefs after re-establishing a normal movement). Even accounting for the active control treatment being potentially less effective than NH-CBT, it seems likely that the mean difference between groups will be small. Our power analysis therefore builds on a conservatively estimated small between-group effect. When designing the control intervention, we also had to consider the pragmatic fact that a treatment-as-usual or a waitlist control group would not have been feasible, because our institution is the only one covering neurorehabilitation for patients from a bigger district in New Zealand, implying limited resources and long waitlists for receiving treatment. Third, another pragmatic limitation is that we have to accept participants in the inpatient and outpatient settings as well as participants of older ages. We will apply statistical strategies to control for the type of treatment setting in our data analysis. We will include older participants only if motor symptoms are considered highly likely to be functional and not related to age-related degenerative processes. Fourth, our 8-week follow-up window after the end of treatment is very short. Again, due to pragmatic reasons associated with delivering both treatments in the context of a clinical service, we would not be able to let our control participants wait for a longer period than this before they receive NH-CBT. At the same time, we consider the *controlled* follow-up assessment as an important strength of our study design. Finally, we will implement several methods to ensure treatment fidelity (e.g., frequent supervision, audio-recording the initial therapy session, and feedback to therapists). However, we will not be able to completely exclude the risk of therapists deviating from our rules of treatment fidelity and exposing participants to distraction techniques or interventions that address illness beliefs.

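### The stated 80% power with 164 participants is for a three-visit interaction, not the week-8 primary contrast, and f = 0.10 on that scale is not a small group difference

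*Protocol article*

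**What the plan says.** The section Sample Size, Power Calculations, and Interim Analyses bases the trial on a group-by-time "interaction effect (*f* = 0.10) under consideration of our three measurements" and "a test-retest reliability of *r* = 0.5". It calls this effect small and the assumption conservative. The mixed-effect ANOVA in G*Power "with an alpha error probability of 0.05 and a power of 0.80 results in an optimal total sample size of 164", which a 5% dropout allowance raises to 172.

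Outcomes and Assessments sets the primary endpoint as SF-36 Physical Functioning at the 8-week follow-up. Statistical Analysis specifies a linear mixed model with baseline adjustment and contrasts to baseline, and states "The outcomes of interest will be the group-by-time interaction at week 8 (hypothesis 1 and 2), and at week 16 (hypothesis 3").

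The Discussion expects a small mean difference from the active control and adds "Our power analysis therefore builds on a conservatively estimated small between-group effect". The article does not give the target effect as a standardized difference or in SF-36 points at week 8.

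**The concern.** Two statements do not describe the primary test. First, the 80% power belongs to an omnibus interaction over baseline, week 8 and week 16. The primary hypothesis rests on one contrast at week 8, for which no power is given. Second, f = 0.10 is small as a label on the f scale, but with three correlated measurements it converts to a group difference well above what most readers would call small.

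What a null result can mean is at stake. The Discussion tells the reader to expect a small advantage over an active comparator and says the trial is sized for one. A reader who accepts that would take a non-significant week-8 result as evidence against such an advantage. The design supports that reading only for differences of roughly 0.4 SD and above.

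**Working it through.** **Inputs from the article.** Two groups, 1:1; m = 3 measurements; r = 0.5; f = 0.10; alpha 0.05; power 0.80; N = 164 before dropout; primary contrast at week 8.

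**Step 1: reproduce 164.** For the G*Power within-between interaction, lambda = f²·N·m/(1 − r) = 0.01 × N × 3/0.5 = 0.06N, with df1 = (2 − 1)(3 − 1) = 2 and df2 = 2(N − 2).
- N = 162: lambda = 9.72, power 0.7998.
- N = 164: lambda = 9.84, power 0.805.

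So 164 is the first even N that reaches 0.80. Other settings do not give it: two measurements give 200, and other effect-size conventions give 484 to 486. The stated number is correct for the 2-df, three-visit interaction.

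**Step 2: convert f = 0.10 to a group difference.** Let δj be the group difference in SD units at visit j. Each cell's interaction effect is ±(δj − mean δ)/2, so over the six cells f² = Σ(δj − mean δ)²/12. Assume no difference at baseline.

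| Profile (baseline, week 8, week 16) | f | Week-8 difference at f = 0.10 |
|---|---|---|
| Sustained (0, δ, δ) | δ/√18 | 0.424 SD |
| Growing linearly (0, δ/2, δ) | δ/√24 | 0.245 SD (δ = 0.490) |
| Half lost by week 16 (0, δ, δ/2) | δ/√24 | 0.490 SD |

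In reverse, a sustained 0.20 SD difference is f = 0.20/√18 = 0.047. At that f the article's own 2-df test has only 24% power with N = 164.

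**Step 3: power of the week-8 contrast.** With 82 per arm, SE = √(4v/164). The variance v is 2(1 − r) = 1.00 for change from baseline (SE 0.156) and 1 − r² = 0.75 with baseline adjustment (SE 0.135). Power is from the noncentral t with 162 df, two-sided 0.05, without allowance for interim looks.

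| Week-8 difference | Change | Baseline-adjusted |
|---|---|---|
| 0.20 SD (assumed) | 25% | 31% |
| 0.245 SD (growing profile) | 34% | 44% |
| 0.30 SD (assumed) | 48% | 60% |
| 0.35 SD (assumed) | 61% | 73% |
| 0.424 SD (sustained profile) | 77% | 88% |
| 0.490 SD (fading profile) | 88% | 95% |

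**Step 4: detectable difference and sensitivity.** With 164 evaluable, 80% power is reached at about 0.44 SD (change) or 0.38 SD (baseline-adjusted). At 0.20 SD, varying r from 0.3 to 0.8 moves power from 19% to 56%. On the normal approximation, 80% power at 0.20 SD and r = 0.5 needs about 786 (change) or 590 (baseline-adjusted) evaluable participants.

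**The case against.** The strongest reply is that nothing is miscalculated. The number 164 reproduces exactly, and for a sustained effect the week-8 test has 77% to 88% power, which brackets the planned 80%. Since the model includes baseline adjustment, the upper figure may apply. This stands: the move from 2 df to 1 df does little harm by itself.

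A reader might infer that the trial simply has 25–31% power for its primary test. The document does not support that. It never states 0.20 SD, and that value is only one reading of the word small. At 0.30 or 0.35 SD the figures are much higher.

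A reader might also infer that comparing f = 0.10 with the earlier trial's f = 0.33 mixes two scales. The article does not say how 0.33 was derived, so this cannot be shown, and 0.10 may still be a cautious choice relative to that trial.

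Finally, the plan will report between-group Cohen's d with 95% confidence intervals, and the Discussion says the interim analyses will check whether the sample-size estimate needs correction. Intervals will limit over-reading of a null result, but neither provision corrects a stated design target that the inputs do not support.

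**Conclusion.** The point holds in a limited form. The 80% power and the 164 describe the omnibus three-visit interaction, not the week-8 contrast that the article makes primary. The effect used is about 0.42 SD at week 8 if sustained, with 0.24 to 0.49 SD under the other two profiles examined. The Discussion's claim of a small between-group effect is therefore not supported by the sizing inputs. The mislabelled effect is the main defect; the mismatch in degrees of freedom is minor.

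The conversion assumes no baseline difference and depends on the time profile. The week-8 powers assume r = 0.5, 164 evaluable participants, two-sided 0.05 and no interim-look correction. The 25–31% figure also requires reading small as 0.20 SD, which is an assumption.

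**What to change.** Keep the sample size and restate the power for the primary test. Suggested wording for the sample-size section:

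> With 164 evaluable participants and r = 0.5, the week-8 group-by-time contrast has 80% power (two-sided 5%, before allowance for interim analyses) for a difference of about 0.44 SD on change from baseline, or about 0.38 SD with baseline adjustment.

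Give the same difference in SF-36 Physical Functioning points under a stated assumed SD. Replace the word small in the sample-size section and in the Discussion with that difference. State the lower power for smaller differences as a range with its assumptions: 25–31% at 0.20 SD, 48–60% at 0.30 SD and 61–73% at 0.35 SD. If the 2-df calculation is kept as background, label it as the omnibus interaction and state the time profile assumed.

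The cost is a reworded power paragraph and one Discussion sentence. No extra participants and no change of analysis are needed, but the stated detectable effect becomes less favourable.

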### Methods for Minimizing Bias

To minimize *selection bias* eligible participants will be randomly assigned to either the NH-CBT or the active control group in a 1:1 ratio using a block randomization strategy (8 blocks with 20 and 1 block with 12 participants). Randomization will be conducted by a research associate not affiliated with the study. The randomization scheme will be generated by using the website randomization.com which applies a pseudorandom number algorithm (http://www.randomization.com). Group allocation will be provided in sealed opaque sequentially numbered envelopes. The principal investigator (MR) and therapists involved in the study will not be masked to the results of the randomization, however the outcome assessors will be blinded to minimize *detection bias*. Before each of the follow-up interviews, participants will be clearly instructed not to discuss treatment content or the identity of their therapists with their assessor. After each follow-up assessment, the blinding of the outcome assessor will be checked with several self-report items (e.g., “Please guess which condition the participant was in”). In the case that the blinding of an outcome assessor cannot be ensured, the three assessor-rated measures will be re-done by a fully blinded assessor. Individual rehabilitation staff will deliver only one of the interventions, either NH-CBT or the control treatment, to reduce the risk of *contamination bias*. Participants from different treatment groups will not be treated in the same room/gym at the same time. Most of our participants will undergo an outpatient treatment and it will be less likely that we have several patients with FNSD receiving inpatient treatment at the same time. It is therefore less likely that participants will communicate with each other about the course of their treatment. Inpatient participants will be instructed not to discuss the details of their treatment with other patients, and inpatient rehabilitation staff will be instructed to remind inpatients of this. To minimize *reporting bias* the study is registered and all pre-specified outcomes are published under the Australian New Zealand Clinical Trials Registry (ANZCTR; identifier: ACTRN12620000550909). To minimize *bias due to loss to follow-up* participants will be sent text reminders on the morning of their appointments. Participants will be considered a dropout when they miss more than two sessions without calling first. Travel costs are not provided directly by the trial but can be reimbursed by other agencies under certain circumstances. Participants will be supported in accessing these reimbursements when eligible.

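### The stated 5% alpha and 80% power do not hold together, because 164 (172 recruited) is a single-analysis sample size with nothing budgeted for the seven earlier efficacy looks.

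*Protocol article*

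**What the plan says.** All of this is in the protocol article under Sample Size, Power Calculations, and Interim Analyses, unless another section is named.

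- Effect and design inputs: "we conservatively assume a small group^*^time interaction effect (*f* = 0.10"), "under consideration of our three measurements and a test-retest reliability of *r* = 0.5".
- Result: a mixed-effect ANOVA "with an alpha error probability of 0.05 and a power of 0.80 results in an optimal total sample size of 164".
- Dropout and recruitment: "A dropout rate of 5% is estimated based on our clinical experience", followed by "Accordingly a sample size of 172 participants is planned to be recruited". Methods for Minimizing Bias randomises the same total "in a 1:1 ratio using a block randomization strategy (8 blocks with 20 and 1 block with 12 participants"), which is 8 × 20 + 12 = 172.
- Looks: "We will, however, allow eight interim analyses every 22nd patient". Table 3 lists them at 22, 44, 66, 88, 110, 133, 155 and 172 patients, with stopping p-values 0.00000003, 0.00009, 0.001, 0.005, 0.013, 0.024, 0.036 and 0.050. The eighth is the analysis of the full sample, so seven come earlier.
- Purpose: the section presents the Lan-DeMets approach as the control on type I error over the repeated looks. Data and Patients' Safety Monitoring confirms that the board may stop the trial for benefit on these rules.

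The article states no change to the sample size or the power on account of the looks.

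**The concern.** A power calculation for one test at 0.05 describes a trial that tests once. When a trial may stop for efficacy at seven earlier points and total alpha is held at 0.05, part of that alpha is used before the end. The last test must then be made below 0.05, and the same number of patients has somewhat less power. Here 164 and 172 come from the single-test calculation, while Table 3 still gives the last look the full 0.050 after allowing rejection at seven earlier looks.

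If the last look keeps 0.050, overall alpha exceeds 5%. If overall alpha is held at 5%, power is below the stated figure. The monitoring board and later readers would be working from operating characteristics that the design does not have.

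**Working it through.** **1. The plan's own figure.** Inputs: f = 0.10, three measurements, correlation 0.5, alpha 0.05, two groups. Sphericity is assumed, as the article does not state it. For the group-by-time interaction:

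λ = f² × N × m / (1 − ρ) = 0.01 × 3 / 0.5 × N = 0.06N, with df 2 and 2(N − 2).

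Power by the noncentral F is 79.98% at N = 162 and 80.5% at N = 164. The next even N is 164, so the figure reproduces, as a single-analysis result.

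**2. After dropout.** 172 × 0.95 = 163.4 evaluable, which gives 80.3% for a single test. This is the starting point for the looks.

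**3. What Table 3 contains.** The O'Brien-Fleming-type spending function gives cumulative alpha 2(1 − Φ(1.96/√t)). The valid nominal p-values for the same function and spacing come from recursive numerical integration.

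| Look, t = k/8 | Cumulative alpha spent | Table 3 | Valid nominal p |
|---|---|---|---|
| 1 | 0.00000003 | 0.00000003 | 0.00000003 |
| 2 | 0.00009 | 0.00009 | 0.00009 |
| 3 | 0.0014 | 0.001 | 0.0013 |
| 4 | 0.0056 | 0.005 | 0.0051 |
| 5 | 0.0132 | 0.013 | 0.0111 |
| 6 | 0.0236 | 0.024 | 0.0186 |
| 7 | 0.0361 | 0.036 | 0.0269 |
| 8 | 0.0500 | 0.050 | 0.0354 |

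The first four rows separate the two columns poorly, and the printed 0.005 fits the cumulative 0.0056 only if truncated. Looks 5 to 8 match the cumulative column and not the nominal one.

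**4. Operating characteristics at the listed sizes.** Information is t = n/172 at the eight listed n, and Z at each look is normal with mean θ√t and variance 1. The drift is set to reproduce the single-test power: θ = 1.960 + Φ⁻¹(0.803) = about 2.81. Two valid versions are shown. A is the function in step 3 used as total two-sided spending of 0.05. B spends 0.025 per side, with cumulative alpha 4(1 − Φ(2.24/√t)).

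| Design | Last-look p | Overall type I error | Power, 172 recruited, 5% lost |
|---|---|---|---|
| One analysis, no looks | 0.050 | 5% | 80.3% |
| Table 3 as printed | 0.050 | 6.5% | about 82% |
| Valid, A | 0.034 | 5% | 78.3% |
| Valid, B | 0.038 | 5% | 78.9% |

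**5. Sensitivity.** With equally spaced looks the type I error of Table 3 is 6.6%. A simulation of the two-degree-of-freedom test, also equally spaced, gives 6.8%, and valid power of 78.5% (A) and 79.1% (B).

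**6. Cost of keeping 80%, for scale.** The inflation factor is 1.051 (A) or 1.036 (B). Recruits needed: 164 × 1.051 / 0.95 = 181.4, or 164 × 1.036 / 0.95 = 178.8.

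**The case against.** The strongest reply is that the plan as written does not fall short of 80%. Table 3 tests the last look at 0.050 and adds seven chances to reject, so power rises to about 82%. This is correct. A reader might infer that 172 recruits simply fail to deliver the stated power, and the article does not support that: a loss appears only after Table 3 is replaced. What the reply does not rescue is the pair of figures. The 82% is reached at a type I error of about 6.5%, against a stated 5%.

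A second reply is that 1 to 2 points is far less than the uncertainty in f = 0.10 and r = 0.5. That stands, and it limits the weight of the power side of the point.

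A reader might also suspect the dropout allowance, since 164 / 0.95 = 172.6 would round up to 173. The article does not say how the 5% was applied. Multiplying gives 164 × 1.05 = 172.2, so the two methods differ by 0.4 of a patient, and power after 5% loss is still 80.3% before any looks. Dropouts may also contribute data, because the Statistical Analysis section uses maximum likelihood and participants who leave treatment are encouraged to complete follow-up. Dropout is not a cause of the problem.

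Finally, a reader might add a further loss because the week-8 contrast, rather than the overall interaction, is the test of interest. That is a separate question about what the calculation targets, and nothing about the looks supports it.

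**Conclusion.** The point holds in a limited form. The single-analysis figures 164 and 172 are reproducible and the dropout step is adequate, but the stated alpha of 0.05 and power of 0.80 cannot both describe a trial with these eight looks. As printed, the design has about 82% power and about 6.5% type I error (6.5 to 6.8% across the methods used). With valid boundaries it has 5% type I error and about 78 to 79% power.

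The excess type I error is the more serious side. The loss of power is 1 to 2 points and is the consequence of putting the boundaries right. These figures assume sphericity, information proportional to the listed sample sizes, O'Brien-Fleming-type spending (inferred from the printed values, since the article names only Lan-DeMets), and no data from the 5% lost, which is pessimistic.

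**What to change.** Replace the Table 3 p-values with nominal stopping levels computed at the listed sample sizes so that overall two-sided alpha is 0.05, and name the spending function. The last level will then be about 0.034 to 0.038, depending on the version chosen. In the same section, restate the power at 172 recruits with 5% loss as about 78 to 79% under those boundaries.

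Alternatively, use fewer looks. Five equally spaced looks with 0.025 per side would put the last test at about p = 0.042 and the power at about 79.4%.

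The cost is one corrected table column and one corrected power statement, ideally before the first interim analysis. No patients need be added. Only if the sponsor wishes to keep 80% would recruitment rise, to about 179 to 182.

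### The look schedule in the text and in Table 3 disagree at looks 6 to 8, and Table 3's thresholds were worked out for equal eighths, not for the sample sizes listed beside them

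*Protocol article*

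**What the plan says.** All of this is in the protocol article, section Sample Size, Power Calculations, and Interim Analyses.

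- Maximum size: "Accordingly a sample size of 172 participants is planned to be recruited". This follows from 164 evaluable participants and 5% dropout.
- Error rate: the power calculation is run "with an alpha error probability of 0.05 and a power of 0.80 results in an optimal total sample size of 164".
- Spacing of looks: "We will, however, allow eight interim analyses every 22nd patient".
- Table 3 pairs eight sample sizes (22, 44, 66, 88, 110, 133, 155, 172) with eight p-values (0.00000003, 0.00009, 0.001, 0.005, 0.013, 0.024, 0.036, 0.050). Its caption describes the p-values as "indicating a necessary stop of the trial and needed sample size at each interim analysis".
- The boundaries are attributed to the Lan-DeMets method. Neither the spending family nor the sidedness is named.

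The section Data and Patients' Safety Monitoring refers the board to these rules for any early stop for benefit.

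**The concern.** The sentence and the table under it give different sizes at three of the eight looks, and the sentence's last look cannot occur within the planned recruitment. A spending-function boundary is also tied to the fraction of information available at the look. If the thresholds were derived for one set of fractions and the looks happen at another, the table does not implement the method that the text names. These figures are the efficacy stopping rule, so the independent analyst and the board need one schedule, fixed before any data are seen.

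**Working it through.** **Inputs.** Maximum 172, total alpha 0.05, the eight sizes and p-values of Table 3, and the 22-patient step, all from the sample-size section. Assumptions: information is proportional to patients, so t = n/172; the tests are two-sided; the spending family is whatever reproduces the printed column.

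**Step 1: the sizes.** The stated step gives 22k for k = 1 to 8, ending at 22 × 8 = 176, which exceeds 172. Table 3 agrees at looks 1 to 5, is one patient higher at looks 6 and 7, and stops at 172. Its increments from zero are 22 (five times), 23, 22 and 17. Eighths of 172 are 21.5, 43, 64.5, 86, 107.5, 129, 150.5 and 172. The listed sizes at looks 2 to 7 exceed these by 1 to 4.5 patients.

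**Step 2: reproduce the printed p-values.** The O'Brien-Fleming-type spending function is A(t) = 2[1 − Φ(1.96/√t)]. For example, at t = 6/8, 1.96/√0.75 = 2.263 and A = 0.0236, printed as 0.024. At the listed look 6, t = 133/172 = 0.773, 1.96/√0.773 = 2.229 and A = 0.0258.

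| Look | 22k | Table 3 n | n/172 | Printed p | A at k/8 | A at n/172 | Nominal boundary p at n/172 |
|---|---|---|---|---|---|---|---|
| 1 | 22 | 22 | 0.128 | 0.00000003 | 2.96e-8 | 4.2e-8 | 4.2e-8 |
| 2 | 44 | 44 | 0.256 | 0.00009 | 0.0000886 | 0.000107 | 0.00011 |
| 3 | 66 | 66 | 0.384 | 0.001 | 0.00137 | 0.00156 | 0.0015 |
| 4 | 88 | 88 | 0.512 | 0.005 | 0.00557 | 0.00614 | 0.0056 |
| 5 | 110 | 110 | 0.640 | 0.013 | 0.0132 | 0.0143 | 0.012 |
| 6 | 132 | 133 | 0.773 | 0.024 | 0.0236 | 0.0258 | 0.020 |
| 7 | 154 | 155 | 0.901 | 0.036 | 0.0361 | 0.0390 | 0.029 |
| 8 | 176 | 172 | 1 | 0.050 | 0.0500 | 0.0500 | 0.034 |

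A at exact eighths reproduces seven of the eight printed values after rounding. Row 4 should round to 0.006. A at n/172 differs from the printed value in each of the first seven rows at the printed precision. Pocock-type spending does not fit: it gives 0.0097 at look 1.

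**Step 3: effect of the fraction mismatch alone.** The nominal boundary c at look k solves P(no earlier crossing and |Z| ≥ c) = A(t_k) − A(t_(k−1)), by recursive numerical integration over independent increments. At exact eighths the nominal p-values are 3.0e-8, 0.00009, 0.0013, 0.0051, 0.011, 0.019, 0.027 and 0.035, with total error 0.0500. The same boundaries applied at n/172 give 0.0489.

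**Step 4: what a repair must avoid.** A(t) is cumulative alpha spent, not a per-look threshold. Used as per-look two-sided p-value thresholds, the printed column gives a total type I error of 0.066 at k/8 and 0.065 at n/172. A(n/172) used the same way gives 0.067. So correcting only the sizes or the fractions does not bring the error back to 0.05.

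**The case against.** The strongest reply is that this is editorial. Each row of Table 3 pairs one size with one p-value, the sentence is a loose summary of a table that governs, and the departures are one patient at two looks plus a cap at the planned maximum. Lan-DeMets spending does not need equal spacing, and the effect on error is slight and conservative.

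Much of that stands. A reader might infer that the table cannot be used at all; it can, row by row. A reader might also infer that the misplaced looks inflate the type I error; taken alone they lower it slightly. What does not stand is the appeal to flexible spacing: the method tolerates unequal looks only when the boundaries are computed at the fractions reached, and these were computed at eighths.

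A reader might go further and take the sentence, the sizes and the p-values for three separate schedules, with the sizes drawn from a maximum near 177. The documents do not support that. No 177 appears, and its eighths fail either way: 110.6 rounds to 111 (printed 110), while 132.75 and 154.9 truncate to 132 and 154 (printed 133 and 155). The sentence and the p-values would even agree at eighths of 176, but 176 is not the planned maximum.

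The fractions n/172 are an assumption. The 172 includes a dropout allowance over 164, and the analysis uses repeated measures with missing data. If the dropout rate is the same at every look, it cancels from the ratio.

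**Conclusion.** The point holds as an internal inconsistency. The sentence and Table 3 cannot both be followed at looks 6 to 8, and the printed thresholds belong to exact eighths instead of the listed sizes. The gap is largest at looks 6 and 7 (0.773 against 0.750, and 0.901 against 0.875). Its own effect on type I error is 0.0489 in place of 0.0500, so it is a minor correction.

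That small figure applies to properly derived boundaries, which Table 3 does not print. The larger error in the column, cumulative spend labelled as stopping p-values, is a separate matter. It is named here because it decides whether the repair works: about 0.065 to 0.067 two-sided if spending values stay as thresholds. Read one-sided, the printed column gives 0.062 to 0.063.

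The conclusion assumes information proportional to patients out of 172 and a spending family inferred from the fit. That row 4 was truncated is one possible explanation and is not shown by the documents.

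**What to change.** 1. Choose one schedule with a maximum of 172: either eighths of 172 in whole patients (22, 43, 65, 86, 108, 129, 151, 172) or the sizes already listed. Replace the 22-patient phrase in the text with those sizes.
2. State the spending function, the sidedness and the information fractions.
3. Rerun the boundary program at the chosen fractions and print the nominal boundary p-values, not the cumulative alpha spent, with enough digits that no row is misrounded. For the listed sizes, two-sided with total alpha 0.05, they are those in the last column of the working table. If the sponsor instead applies the O'Brien-Fleming-type function to each tail at 0.025, they become about 7.4e-10, 0.000019, 0.00059, 0.0033, 0.0090, 0.018, 0.029 and 0.038.
4. If a look falls at a different size in practice, recompute its boundary at the fraction reached.

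The cost is one rerun of the program, one corrected table and one corrected sentence. The planned sample size of 172 does not change. The corrected thresholds at looks 5 to 8 are stricter than those now printed.
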